### Outcome measures

2.7

(1)Validity index: The primary outcome is a combination of total VTE (venography or symptomatic DVT and/or PE) and all-cause mortality during treatment, which is defined as the time from the date of the first study to 3 days after the last administration, and the secondary outcome is a combination of major VTE (venography or symptomatic proximal DVT and/or PE) and VTE-related mortality during treatment.(2)Security index: The main safety outcome is the incidence of massive hemorrhage from the first medication in the study to 2 days after the last use (continued treatment). Massive hemorrhage is defined as clinically fatal bleeding that occurs in critical organs (such as retroperitoneal, intracranial, intraocular, or intraspinal), requiring surgery, outside the surgical site, and associated with it. The secondary safety outcome was the incidence of clinically related non-major bleeding events, defined as polyphyly hemorrhage, accidental hematoma (>25 cm^2^), excessive wound hematoma, epistaxis (>5 min), gingival bleeding (>5 min), gross hematuria, rectal bleeding, cough or hematemesis, vaginal bleeding, semen bleeding, traumatic intra-articular bleeding, or surgical site bleeding, etc. Secondary safety outcomes also include the incidence of adverse reactions, such as abnormal laboratory indicators (with special emphasis on liver and kidney function indicators), allergic reactions, and other adverse events.

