### Interventions

2.6

Before operation, the patients were examined by Doppler ultrasound to determine whether there was venous embolism, and if necessary, additional pulmonary CT was taken to rule out pulmonary embolism. The rivaroxaban group began to take 10 mg, once a day, 6 to 8 hours after operation, while the dabigatran etexilate group began to take 1 to 4 hours after operation, which was halved at the first time, and recovered to 220 mg once a day the next day. Both course of treatments lasted for 2 weeks.

Ultrasonic Doppler examination of limbs was performed by ultrasound doctors at 1 or 2 weeks after operation. If the formation of DVT is suspected, ultrasonic Doppler examination should be performed immediately; if pulmonary embolism is suspected, pulmonary CT or angiography should be performed in addition to ultrasonic Doppler examination, and the results should be recorded. The patients were followed up for 30 to 35 days after the last administration. Hematological examination was performed before operation, on the same day after operation and before discharge, and abnormal laboratory indexes were monitored. Hematological and imaging tests could also be performed during follow-up if necessary.

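### Both efficacy outcomes admit a DVT only by venography or symptoms, but the only DVT imaging described is Doppler ultrasound, so a silent DVT on the scheduled scan is not an event as written

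*Protocol article*

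**What the plan says.** Section 2.7 (Outcome measures) builds the primary outcome from "total VTE (venography or symptomatic DVT and/or PE) and all-cause mortality during treatment". The secondary efficacy outcome follows the same pattern: "the secondary outcome is a combination of major VTE (venography or symptomatic proximal DVT and/or PE) and VTE-related mortality during treatment". In both, a DVT can enter by two routes only: it is shown on venography, or it is symptomatic.

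Section 2.6 (Interventions) describes the imaging:

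- Baseline: "Before operation, the patients were examined by Doppler ultrasound to determine whether there was venous embolism", with CT of the lungs added where needed. Section 2.4 (Patients) also relies on colour Doppler for eligibility.
- Scheduled, after surgery: "Ultrasonic Doppler examination of limbs was performed by ultrasound doctors at 1 or 2 weeks after operation".
- On suspicion of DVT: "If the formation of DVT is suspected, ultrasonic Doppler examination should be performed immediately".
- On suspicion of PE: "if pulmonary embolism is suspected, pulmonary CT or angiography should be performed in addition to ultrasonic Doppler examination".
- During follow-up, further imaging is allowed where needed, with no method named.

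Venography is not mentioned in any of these procedures.

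**The concern.** The definition and the ascertainment do not match. A routine scan of all patients is evidently there to find DVT that has not announced itself, because a suspected DVT already triggers its own immediate Doppler. Yet a silent DVT found on that scan satisfies neither route into the outcome.

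What is at stake is which events make up the primary outcome. Someone classifying events must either follow the text and leave silent Doppler findings out, or count them and report an outcome other than the one defined. Two analysts working from the same article could arrive at different event counts. The word venography also suggests that the rates can be set beside venographic rates, which the described procedures do not support.

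**Working it through.** This is mainly a comparison of text. The article states no event rate on prophylaxis, no effect size and no power, so there is no planned figure to reproduce.

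**Step 1. Match each way of finding an event to the definition in 2.7.**

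| Finding | Method described in 2.6 | Event under 2.7, read literally? |
|---|---|---|
| DVT with symptoms | Doppler | Yes (symptomatic) |
| DVT without symptoms, on the scheduled scan | Doppler | No: neither venographic nor symptomatic |
| PE, suspected and confirmed | CT or angiography plus Doppler | Yes |
| Death from any cause | – | Yes (primary outcome) |

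The same holds for the secondary outcome, restricted to proximal DVT and VTE-related death. The angiography in 2.6 is tied to suspected PE and does not serve as limb venography.

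**Step 2. Check that timing does not explain the gap.** The course lasts 2 weeks and the outcome window closes 3 days after the last dose, at about day 14 + 3 = 17. A scan at 1 or 2 weeks falls inside the window, so silent findings are not excluded on timing.

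**Step 3. Illustrate what could hang on the choice.**

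From the article: 300 per group (2.3), Fisher's exact test for categorical outcomes and a threshold of 0.05 (2.9). Sidedness is not stated; two-sided is assumed.

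Assumed, with no support in the article: DVT in 10% of one group and 5% of the other (a halving); 50% to 80% of DVTs silent, equally in both groups; DVT only, leaving out PE and deaths.

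Countable rate = DVT rate × (1 − silent fraction):

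- 50% silent: 10% × 0.5 = 5%, and 5% × 0.5 = 2.5%
- 80% silent: 10% × 0.2 = 2%, and 5% × 0.2 = 1%

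Expected events = 300 × (p1 + p2). Exact power = the sum, over all pairs of counts (i, j), of Bin(i; 300, p1) × Bin(j; 300, p2), taken where the Fisher P value is below 0.05.

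| Countable DVT rates | Expected events | Fisher power |
|---|---|---|
| 10% v 5% (all DVT counted) | 300 × 0.15 = 45 | 0.593 |
| 5% v 2.5% (50% silent, not counted) | 300 × 0.075 = 22.5 | 0.296 |
| 2% v 1% (80% silent, not counted) | 300 × 0.03 = 9 | 0.090 |

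PE and deaths remain countable under either reading, so the composite would hold more events than the lower rows show.

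**The case against.** The best reply is that this is loose wording. The English is uneven throughout, and venography may have been meant simply as imaging of the veins, in which case Doppler findings were always intended to count. That is plausible, but the text does not settle it: the article names Doppler explicitly in 2.4 and 2.6 and uses a different word in 2.7. Intent that has to be guessed is a poor basis for a primary outcome.

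Several stronger readings are tempting and are not supported:

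- *The trial performs no venography.* The article only describes none. It condenses a full protocol that is not shown, and 2.6 allows unspecified imaging during follow-up. That clause does not provide systematic venography, so the mismatch remains.
- *The scheduled scan contributes nothing.* Even on the literal reading it can confirm DVT in a patient who has symptoms.
- *Most events are lost.* That depends wholly on the silent fraction, which the article does not give. The Introduction's figures (40% to 60% DVT and 1% to 2% PE) are for patients without medication and do not carry over to two treated groups.
- *The outcome will be changed after results are seen, or the comparison is biased.* Nothing shows either. The definition applies equally to both groups, and 2.5 states that clinicians, researchers and the analysing statisticians are blinded.
- *Planned power is lost.* Section 2.3 calls the study exploratory and states no power.

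It is also fair to say that the article alone does not show which of 2.6 and 2.7 holds the slip.

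**Conclusion.** The inconsistency stands and depends on no assumption: sections 2.6 and 2.7 disagree on how a DVT becomes an outcome event, in both efficacy outcomes. It is a conflict between stated passages, not a detail that could be left to an analysis plan. Because it determines which primary events are counted, it needs correcting.

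Its size cannot be derived from the documents. The fall in power from 59% to 30% or 9% is illustrative only. It rests on an assumed 10% DVT rate, an assumed halving between two active drugs, an assumed silent fraction of 50% to 80%, and DVT alone. A smaller effect would lower the power at each rate; PE and deaths would restore some events. The demonstrated harm is ambiguity about the primary outcome, with a possible loss of events.

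**What to change.** Before outcome data are examined, reconcile sections 2.6 and 2.7, and the registration with them, so that both outcomes name the imaging actually used:

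- **Total VTE (primary):** any DVT, asymptomatic or symptomatic, on the protocol Doppler examination, or PE confirmed by CT or angiography; combined with death from any cause.
- **Major VTE (secondary):** proximal DVT by the same method, or PE; combined with VTE-related death.

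Replace the word venography unless it is in fact performed under the full protocol. If it is, section 2.6 should describe it, and section 2.7 should still say whether a silent DVT seen on Doppler counts. Since 2.6 places the scheduled scan at 1 or 2 weeks, the amended definition should also say which examination it refers to.

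The cost is an amendment to the wording and the registration, with no new procedure. The downside is that results could not be described as venographic rates or compared directly with them.

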### Study design

2.5

Eligible participants were randomly assigned to the rivaroxaban oral group or dabigatran etexilate oral group in a 1:1 ratio using a central network-based random tool. The random sequences are generated by SAS 9.3 software (SAS Institute, Cary, NC) by independent statisticians who do not participate in trial implementation or statistical analysis. Randomization was performed without any stratification. The clinical research coordinator entered participant information on the tablet and was given a random number. The research assistant obtained the allocation of participants from the computer. Throughout the study, the research assistant was responsible for screening, recruiting participants, and assigning random numbers to participants who had been included. Results evaluator was responsible for the evaluation of the scale. The grouping of personnel is unknown to all clinician, researchers, research assistants, participants, intervention supervisors, and statisticians who conduct statistical analysis. The drugs were distributed by unwitting nurses to patients with corresponding numbers according to the drug number.

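### Massive hemorrhage is counted from the first dose, which the protocol schedules 2 to 7 hours earlier for dabigatran than for rivaroxaban, so bleeds in that gap count in one arm only

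*Protocol article*

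**What the plan says.** Section 2.7 (Outcome measures) fixes the counting window for the main safety outcome: "The main safety outcome is the incidence of massive hemorrhage from the first medication in the study to 2 days after the last use". The start of the window is therefore each patient's own first dose.

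Section 2.6 (Interventions) sets that first dose differently by arm. For rivaroxaban: "The rivaroxaban group began to take 10 mg, once a day, 6 to 8 hours after operation". For dabigatran: "the dabigatran etexilate group began to take 1 to 4 hours after operation". Duration is common to both: "Both course of treatments lasted for 2 weeks".

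Three further statements bear on how far the problem reaches:

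- The definition of massive hemorrhage in section 2.7 contains the phrase "requiring surgery, outside the surgical site, and associated with it". The wording is garbled, but it may exclude bleeding at the surgical site.
- The next outcome is introduced with "The secondary safety outcome was the incidence of clinically related non-major bleeding events". Its list includes wound hematoma and surgical-site bleeding, and no counting window is stated for it.
- Section 2.5 (Study design) claims wide blinding and says of supply: "The drugs were distributed by unwitting nurses to patients with corresponding numbers according to the drug number". Neither there nor in section 2.6 is a placebo or double-dummy mentioned.

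**The concern.** The trial compares two regimens that start at different times after the same kind of operation. Some bleeding in the first hours after surgery would occur in either arm whatever the drug. When the window is tied to the first dose, a stretch of those hours is observed for outcome purposes in the dabigatran arm and not in the rivaroxaban arm. Randomisation does not balance this, because the imbalance lies in when counting starts and not in who is enrolled. A larger sample does not remove it either. The direction is known: it makes dabigatran look worse. Safety is half of the stated aim, and this is its main outcome.

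**Working it through.** The plan gives no figure for this offset, for the bleeding rate or for the timing of bleeds, so there is nothing of its own to reproduce. The check goes from the stated schedule to the offset, and then to a range under stated assumptions.

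**Inputs from the protocol article.** First dose at 1 to 4 h (dabigatran) and 6 to 8 h (rivaroxaban), two weeks of treatment (section 2.6). Counting from first dose to 2 days after last use (section 2.7). 300 patients per arm (section 2.3). Fisher's exact test at 0.05 (section 2.9; taken here as two-sided, which the section does not state).

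**Offset in window start** = rivaroxaban start minus dabigatran start.

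- Smallest: 6 - 4 = 2 h
- Midpoints: 7 - 2.5 = 4.5 h
- Largest: 8 - 1 = 7 h

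The two ranges do not overlap, so for patients dosed on schedule the dabigatran window always opens first. A qualifying bleed at hour 5 is inside the window for every such dabigatran patient and outside it for every such rivaroxaban patient.

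**Gap as a share of the window.** Assuming 14 once-daily doses, the window lasts 13 x 24 + 48 = 360 h. The gap is 2/360 = 0.6% to 7/360 = 1.9% of it.

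**Effect on the ratio.** Let both arms have the same true risk p, and let a share f of bleeds fall in the gap. The expected counted ratio, dabigatran to rivaroxaban, is p / [p(1-f)] = 1/(1-f).

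- Bleeds evenly spread: f = 0.0056 to 0.0194, ratio 1.006 to 1.02.
- f = 0.10, 0.20, 0.30 (assumed early clustering): ratio 1.11, 1.25, 1.43.

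The formula gives rivaroxaban no credit for a window that also closes later relative to surgery. If bleeds really were evenly spread, those late hours would roughly offset the lost early ones, so 1.006 to 1.02 is an upper value for that case. If bleeds cluster soon after surgery, hours about two weeks later do not make up for the loss.

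**Counts and test behaviour at 300 per arm, equal true risk.** All values of p and f are assumptions.

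| p | f | Expected counted bleeds, dabigatran v rivaroxaban | Ratio | Chance of Fisher p < .05 | Same, no offset |
|---|---|---|---|---|---|
| 1% | 25% | 3.0 v 2.25 | 1.33 | 1.3% | 1.2% |
| 2% | 10% | 6.0 v 5.4 | 1.11 | 2.5% | 2.3% |
| 2% | 25% | 6.0 v 4.5 | 1.33 | 3.6% | 2.3% |
| 2% | 50% | 6.0 v 3.0 | 2.00 | 9.0% | 2.3% |
| 5% | 25% | 15.0 v 11.25 | 1.33 | 8.2% | 3.2% |

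At 5% and f = 10 to 30%, the uncounted rivaroxaban bleeds number 300 x 0.05 x f = 1.5 to 4.5. At low rates the test hardly moves; the point estimate is shifted by the same ratio whatever the rate.

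**With a common origin** the offset is 0 h, and the expected ratio under equal risk returns to 1.0.

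**The case against.** Several points on the other side have weight.

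*The outcome may be too narrow for this to matter much.* The stated window belongs to massive hemorrhage only. If its definition excludes surgical-site bleeding, many early post-operative bleeds are not events in either arm, and f is small. This stands as a limit on size. Critical-organ bleeds in the gap would still be treated unequally. The non-major outcome, which does list wound and surgical-site bleeding, would be affected more, but only if it uses the same window, and the article does not say that it does.

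*A double-dummy would remove the offset.* Dummy doses at both times would give every patient a first study medication at 1 to 4 hours. The blinding claimed in section 2.5 is hard to square with different start times unless dummies are used, and a condensed article may have left them out. This also stands: the bias follows from the text as written, not from every way the trial could be run. A reader might infer that blinding could not cure the problem; blinding by double-dummy would.

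*First dose to last dose plus a margin is a recognised on-treatment safety window.* It is. It suits a comparison in which both arms start together. Here the start time is part of what differs between the regimens, so the window excludes part of the difference under study. It remains reasonable as a sensitivity analysis.

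*Withheld doses.* A reader might infer that a rivaroxaban patient whose first dose is withheld because of an early bleed drops out of the safety comparison altogether. No section describes withholding a first dose or defines a safety population, and the latter is commonly left to the full protocol or analysis plan. The point does not rest on this.

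**Conclusion.** The concern holds in a limited form. On the written schedule, with no dummy dosing described, the window for massive hemorrhage opens 2 to 7 hours earlier for dabigatran, and qualifying bleeds between the two first-dose times are counted in that arm only. The direction is certain on that reading; the size is not. It runs from close to no distortion (a ratio of at most about 1.02) if bleeds are evenly spread, to 1.11 to 1.43 if 10 to 30% of them fall in the gap. Nothing in the document supports one share over another, so the upper figures are illustrations and not estimates.

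A reader might go further and say that early post-operative bleeding in general counts against dabigatran. The text does not support that: bleeds before the dabigatran dose count in neither arm, the stated window covers massive hemorrhage only, and the definition of that outcome may leave surgical-site bleeding out.

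**What to change.** In section 2.7, state that major and non-major bleeding are counted, for every randomised patient who is operated on, from one common time point in both arms (for example the end of surgery), whatever the time of the first dose. Keep the first-dose window as a sensitivity analysis. Because the end of the window is tied to the last dose, the sentence should also say when counting ends for an operated patient who takes none.

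Reconcile sections 2.5, 2.6 and 2.7 on whether dummy doses give both arms the same first-medication time. If they do, say so, and the offset disappears. Clarify in the same edit whether the phrase about the surgical site in the definition of massive hemorrhage is meant as an exclusion, since that decides how many early bleeds are in play.

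The cost is a sentence or two. The downside is small: some bleeds before any study drug are counted, but in both arms alike. No change to either dosing schedule is implied.

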### Sample size

2.3

The aim of this prospective study was to explore a comparison of the efficacy and safety of rivaroxaban and dabigatran etexilate in preventing venous thrombosis after joint replacement. The exploratory of this study does not necessarily require formal sample size calculations. So, based on past clinical experience and previous studies,^[9]^ the sample size of 600 participants (300 in each group) was sufficient to achieve the actual purpose of the trial.

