### Statistical analysis

2.9

Data were analyzed using the statistical software package SPSS version 25.0 (Chicago, IL). Continuous variables were described as the mean ± standard deviation, and differences between groups were analyzed using a series of one-way analysis of variance (ANOVA) with Bonferroni's post-hoc test, while differences between groups over time were analyzed using multi-way ANOVA with Bonferroni's post-hoc test. Categorical variables were described as the number (%), and were analyzed by Fisher's exact test. A *P* value of <.05 was considered statistically significant.

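### The main safety outcome, massive hemorrhage, is defined in one sentence that works neither as joint conditions nor as alternatives, and its boundary with non-major bleeding is open

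*Protocol article*

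**What the plan says.** All of this stands in the protocol article, mainly in section 2.7 (Outcome measures).

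- **Outcome and window:** "The main safety outcome is the incidence of massive hemorrhage from the first medication in the study to 2 days after the last use".
- **Definition of massive hemorrhage:** "clinically fatal bleeding that occurs in critical organs (such as retroperitoneal, intracranial, intraocular, or intraspinal), requiring surgery, outside the surgical site, and associated with it". No other section gives another definition or a supplementary criterion.
- **Next category down:** "The secondary safety outcome was the incidence of clinically related non-major bleeding events". An open list follows. It includes wound hematoma, epistaxis and gingival bleeding lasting more than 5 minutes, and ends with "traumatic intra-articular bleeding, or surgical site bleeding, etc". Other adverse events form a further secondary safety outcome.
- **Size (section 2.3):** 300 patients per group. The article says that the study "does not necessarily require formal sample size calculations" and gives no bleeding rate.
- **Analysis (section 2.9):** "Categorical variables were described as the number (%), and were analyzed by Fisher's exact test", with significance at P<.05.

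**The concern.** The base term of the definition is fatal bleeding. Critical organ, need for surgery and location outside the surgical site all hang on it as qualifiers, and the list closes with *and*. The only *or* sits inside the bracketed organ examples. The last element points to an *it* that the sentence never identifies.

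An assessor who follows the text would leave serious bleeds out of the main safety outcome. An assessor who takes the elements as a list of alternatives would count trivial ones. Two assessors could classify the same bleed differently, and both could cite the protocol.

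Safety is half of the trial's stated purpose. Section 2.6 also starts the two drugs at different times after operation (6 to 8 hours v 1 to 4 hours), so early bleeding at the operated site is a plausible place for the groups to differ. On the literal reading, the main safety outcome excludes that site.

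**Working it through.** **Step 1. Apply both readings to example bleeds.** The article states no figure that depends on this definition, so there is none to reproduce. The test is whether either reading sorts bleeds sensibly.

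| Bleed | All conditions required | Any one sufficient | Place in the non-major list |
|---|---|---|---|
| Intracranial, non-fatal | Not major (not fatal) | Major | Not named; only through *etc.*, or as another adverse event |
| Fatal, not in a critical organ | Not major | Major | Not named as such |
| Surgical site, reoperated, patient survives | Not major (not fatal, not outside the site) | Major (required surgery) | Named: surgical-site bleeding, with no upper severity limit |
| Epistaxis over 5 minutes | Not major | Major (outside the surgical site) | Named |

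The joint reading loses the first three rows. The any-one reading puts the last two rows in both categories. If the closing clause is taken to restrict only the outside-the-site element, the epistaxis row depends on a condition that cannot be applied, because *it* is undefined.

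**Step 2. Illustrate the literal reading.** Inputs: n = 600 in total, 300 per group (section 2.3); Fisher's exact test at .05 (section 2.9), taken as two-sided because the article does not say. The risk p of an event that meets all conditions is an assumption, equal in both groups.

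Expected events = 600 × p. Chance of no event in the trial = (1 − p)^600.

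| Assumed p | Expected events | Chance of none |
|---|---|---|
| 0.02% | 600 × 0.0002 = 0.12 | 0.9998^600 = 0.887 |
| 0.05% | 600 × 0.0005 = 0.3 | 0.9995^600 = 0.741 |
| 0.1% | 600 × 0.001 = 0.6 | 0.999^600 = 0.549 |
| 0.2% | 600 × 0.002 = 1.2 | 0.998^600 = 0.301 |
| 0.5% | 600 × 0.005 = 3.0 | 0.995^600 = 0.049 |

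**Step 3. What the planned test could show.** With 300 per group, 0 v 5 events gives P = 0.061 and 0 v 6 gives P = 0.030. At least six events, all in one group, are needed when the other has none. If one group has risk p and the other 2p, power is below 0.1% for p from 0.05% to 0.2%, and about 2% at p = 0.5%.

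Zero events in a group of 300 would still allow a true risk up to 1 − 0.025^(1/300) = 1.2% (one-sided 97.5% limit). An empty table would therefore not be evidence that the drugs bleed equally.

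**Step 4. Would an any-one rule rescue the test?** At an assumed any-one risk of 1%, about 600 × 0.01 = 6 events are expected. Power for 1% v 2% is about 9%. The rewording makes the outcome meaningful; it does not make the comparison well powered.

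**The case against.** The strongest reply is that the sentence is visibly corrupted, so it has no settled conjunctive meaning. The sponsor probably intended alternatives and lost the separators, and competent assessors would apply them that way. This stands in part. A reader might infer that the main safety comparison is bound to end near 0 v 0 whatever happens. That follows only if assessors apply the strict reading, and the article does not show that they will. The reply does not save the definition, however. Nothing in the article says that alternatives were meant, and the any-one reading fails too, by the epistaxis example and the unfinished clause.

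Three other tempting inferences also go beyond the article:

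- **Intracranial bleeds pooled with nosebleeds.** The non-major list names no critical-organ bleed. Such a bleed enters only through *etc.* or falls under other adverse events. What can be shown is that it has no clear category. The mixing is supported for reoperated surgical-site bleeds only.
- **A numeric threshold lost after the last clause.** Section 2.7 gives no sign that the missing object was numeric. It may have referred to the operation or to the site.
- **A null result caused by the wording.** Step 4 shows that a non-significant result would remain likely at an assumed 1% risk under a sound definition, in a study that calls itself exploratory.

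Two further replies carry little weight. A journal article condenses the full protocol, but this one prints a definition rather than leaving it out. An analysis plan would also come late for a rule that governs how bleeds are recorded and classified during the trial.

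**Conclusion.** The point holds as a defect of a stated rule. Followed literally, the definition excludes non-fatal critical-organ bleeds and reoperated surgical-site bleeds; taken as alternatives, it makes listed minor bleeds major. The closing clause cannot be applied on either reading, and the boundary with non-major bleeding is open. That conclusion rests on the wording of section 2.7 alone.

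The size is illustrative. If the all-criteria risk is 0.02% to 0.1%, 600 patients yield 0.1 to 0.6 expected events, with an 89% to 55% chance of none, and the main safety result would say little about the drugs. These rates are assumptions. The article supports neither a prediction of what the assessors will do nor a claim that better wording would give adequate power. The definition should be corrected before any bleed is classified.

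**What to change.** Amend section 2.7 and the case report form as follows:

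1. Define massive hemorrhage as bleeding that meets **any one of**: (a) fatal; (b) in a listed critical organ; (c) requiring surgery; (d) outside the surgical site together with whatever criterion the sponsor intended in the last clause. If no such criterion was intended, delete (d).
2. State expressly how surgical-site bleeding that requires surgery is classified, since the current text both excludes the site and names the need for surgery.
3. Define non-major bleeding as bleeding on the list that meets no major criterion, and replace *etc.* with a closed list, so that no bleed falls in two categories.

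The cost is a change of wording and of the form. Items (a) to (c) should need little beyond the record of each bleed. Whether (d) needs more data depends on what is restored. If it is laboratory-based, section 2.6 schedules blood tests only before operation, on the day of operation and before discharge (otherwise as necessary), while the outcome window runs to 2 days after the last dose.
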